**SECTION 3 – HUMAN SUBJECTS**

**3.1 SUBJECT POPULATION**

Subjects for this investigation will be recruited without regard to gender, race, or ethnic background. The anticipated age range for the study population will be >18 years old based upon the target disease population. The study population will be recruited from the inpatient populations at UPMC.

Ten adult subjects of both genders and all ethnic backgrounds with acute IPF exacerbations hospitalized will be eligible for enrollment. All subjects must provide written informed consent prior to participation. Surrogate consent will be obtained for subjects on mechanical ventilation, until the subjects are able to confirm the consent process when they are able to communicate. Based on the referral populations of UPMC, we expect ~40% of eligible subjects will be women and ~10% will be non-Caucasian.

We should be able to achieve these recruitment goals, as the number of potentially eligible patients is far greater than these projected numbers (42 IPF exacerbations at UPMC in the past fiscal year). We anticipate too that nearly all eligible subjects (or their surrogates) will likely elect to participate in this trial, given the poor response to current treatment.4 We expect to enroll the proposed study population within one calendar year.

**3.1.1 Inclusion of Women and Minority**

Women who meet the inclusion criteria, and have none of the exclusion criteria, will be enrolled without restriction as dictated by the study protocols. Because of the use of a study medication, woman of child bearing potential must meet specialized inclusion/exclusion criteria to minimize this risk. We will make efforts to enroll participants in this research in a distribution which mirrors the study population of the Pittsburgh area.

**3.1.2 Inclusion of Children**

This investigation will not enroll children based upon to target disease population.

**3.2 INCLUSION CRITERIA**

The inclusion criteria have been selected to isolate a patient population with advanced idiopathic pulmonary fibrosis with a disease exacerbation. The exclusion criteria are selected to not enroll patients with an alternative cause for a respiratory decompensation (ie infection, pulmonary embolism) and to exclude patients with increased risk for the associated intervention (corticosteroids, plasmapheresis and ritiximab). Patients with a coagulopathy are excluded to minimize the risk of catheter insertion associated with the intervention.

1) A diagnosis of idiopathic pulmonary fibrosis that fulfills American Thoracic Society Consensus Criteria.1*

2) Unexplained worsening or development of dyspnea or hypoxemia within 30 days leading to the current hospitalization.

3) Radiographic imaging showing ground-glass abnormality and/or consolidation superimposed on a background of reticular or honeycomb pattern consistent with UIP.

4) Intent on the part of the treating physician to use high dose steroid therapy as a therapeutic effort to treat a diagnosis of acute IPF exacerbation.

In addition to strict adherence to current consensus criteria,1 IPF patients have serologic determinations of antinuclear antibody (ANA), rheumatoid factor (RF), anti-glomerular basement membrane antibody (AGBM), and anti-nuclear cytoplasmic antibodies (p-ANCA and c-ANCA) as standard of care diagnostic tests. Results of these serologic tests will be retrospectively used to substantiate the absence of confounding autoimmune syndromes in trial subjects, with implications for final data analyses and reporting.

**3.3 EXCLUSION CRITERIA**

1. Diagnosis of documented infection based upon clinical evaluation and microbial testing.
2. Diagnosis of thromboembolic disease by clinical assessment.
3. Diagnosis of an additional etiology for ALI/ARDS based upon clinical assessment to include sepsis, aspiration, trauma, inhalational injury, acute pancreatitis, drug toxicity, blood product transfusion reaction, or stem cell transplantation.
4. Diagnosis of congestive heart failure that accounts for the hypoxemia.
5. Presence of active hepatitis B infection.
6. Coagulopathy defined as an INR > 1.8, PTT > 2 x control, and platelet count < 50K.
7. Hyperosmolar state or diabetic ketoacidosis to suggest uncontrolled diabetes mellitus or uncontrolled hypertension (systolic BP > 160 mm Hg and diastolic BP > 100 mm Hg) which would contraindicated the use of corticosteroids.
8. Hemodynamic instability defined as a vasopressor requirement which would contraindicate the use of plasmapheresis.
9. History of reaction to blood products, murine-derived products, or prior exposures to human-murine chimeric antibodies,
10. History of malignancy.
11. Inability or unwillingness to accept a blood transfusion.
12. Inability or unwillingness to complete post- treatment surveillance for 60 days.
13. Diagnosis of major comorbidities expected to interfere with subjects study participation for 60 days.

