**2.2 DETAILED DESCRIPTION OF RESEARCH ACTIVITIES**

**2.2.1 Study Design and Procedures**

The proposed combined treatment of plasma exchange (PEX), rituximab, and corticosteroids is routinely provided for a specific subset of patients with a unique form of autoimmune interstitial lung disease, called anti-synthetase syndrome or anti Jo-1 antibody syndrome at UPMC PUH. In this proposal, we plan to extend this treatment to the more general IPF exacerbation patient population which currently is most commonly treated with high dose corticosteroids or pulse solumedrol alone. All clinical and laboratory testing will be considered part of routine medical care for patients with no therapeutic options and a very high recognized mortality rate. In addition to routine medical care, specific T-cell and B-cell assays will be conducted in the laboratory of a Co-PI ([name]).

After hospital admission for acute IPF exacerbation (and after informed consent is obtained), subjects will receive the standard steroid treatment followed by initiation of the PEX and rituximab regimens. These latter two agents will require insertion of a dialysis/apheresis catheter into a central vein.

Standard Steroid Treatment: One gm of methylprednisolone i.v., on day 0, followed by 40 mg/day i.v. on days 1-4, and days 6-12 (or the p.o. prednisone equivalent). Methylprednisolone 100 mg i.v. will be administered on days 5 and 13. Steroid doses will then be 20 mg methylprednisolone i.v. (or p.o. prednisone equivalent) from days 14-28, and then reduced thereafter at the discretion of the principle investigator at each site. There are no published data that show efficacy of this agent at these doses. Nonetheless, steroid treatments (with highly varied doses and durations) are currently the standard of care for IPF patients with acute exacerbations.4 The high initial dose is intended to optimize early lympholysis. Administration of methylprednisolone 100 mg i.v. on days 5 and 13 will standardize steroid treatments among the two trial arms, as these agents are recommended prior to rituximab infusions.78 Steroid doses < 20 mg methylprednisolone i.v. (or p.o. prednisone equivalent) from days 14-28 are important to establish as this dose is an appropriate cutoff for consideration of lung transplantation.

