Plasma exchange (PEX) will consist of 1.5x estimated plasma volume exchanges for 3 successive days (0, 1,2) and then, after a one day interval to enable equilibration of autoantibodies sequestered in tissues, two more daily treatments on days 4 and 5. It is anticipated that fluid replacement with 5% albumin:normal saline (3:1 ratio), with a net fluid balance of 95-100%, will be possible in nearly all patients for the first two treatments. In the event a subject’s INR is >1.5 at the initiation of a PEX treatment, as may occur on the third or later treatment, the albumin:saline replacement will be partially supplanted with fresh frozen plasma (FFP) (anticipated to be <10 U/treatment) to maintain INR <1.6. The dialysis catheter will be removed after completion of the 5th and final PEX.

Rituximab: One gm i.v. will be administered on day 5 (after completion of the last PEX) and day 13. This regimen is adopted from the protocol of a recent large myositis trial at UPMC and other sites (NIHNO1 AR42273) and was well tolerated. Subjects will be treated with acetaminophen, antihistamines and methylprednisolone 100 mg i.v. prior to administration of rituximab to obviate reactions.75

The study design and flowchart is outlined in the table below (Appendix 1).

| Combined Treatment | **Days on Interventions** | | | | | | | | | |
| --- | --- | --- | --- | --- | --- | --- | --- | --- | --- | --- |
| **0** | **1** | **2** | **3** | **4** | **5** | **6-12** | **13** | **14-28** | **> 28** |
| Steroids | 1 gm /day, IV | 40 mg/day, IV  or oral Prednisone equivalent | | | | 100 mg  /day, IV | 40 mg/day, IV  or oral Prednisone equivalent | 100 mg  /day, IV | 20 mg/day, IV  or oral Prednisone equivalent | Tapering thereafter at the discretion of the treating physician |
| Plasma Exchange | 1.5x estimated plasma volume exchange/day | | | NA | 1.5x estimated plasma volume exchange/day | | NA | | | |
| Rituximab | NA | | | | | 1gm  /day, IV | NA | 1 gm  /day, IV | NA | |

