A telephone contact will occur on Day 60 for post treatment survival surveillance. If the subject remains inpatient, the assessment may be completed in the hospital setting. Subjects will be contacted by the study personnel to assess for symptoms potentially related to adverse effects of medications, review of medication changes, and interval medical or surgical histories including emergency or physician office visits. A variance of 3 days will be allowed for the telephone contact to facilitate scheduling or to account for weekends or holidays.

The schedule for patient assessment is outlined as follows (Appendix 2).

Day 0 (Enrollment):

- Informed Consent
- History and physical exam to include vital signs and blood pressure.
- Laboratory evaluations including complete blood count (CBC), electrolytes, glucose, BUN, serum creatinine, calcium, magnesium, phosphorus, albumin, liver function tests, and INR.
- Serology for hepatitis B (HbsAg).
- Assessment of PaO2.
- Complement studies of C3, C4, CH50.
- Assessment of peripheral blood T-cell and B-cell assays .

Day 7:

- Brief history and physical exam to include vital signs and blood pressure.
- Laboratory evaluations including complete blood count (CBC), electrolytes, glucose, BUN, serum creatinine, calcium, magnesium, phosphorus, albumin, liver function tests, and INR.
- Assessment of PaO2.
- Complement studies of C3, C4, CH50.
- Assessment of peripheral blood T-cell and B-cell assays.

Day 14:

- Brief history and physical exam to include vital signs and blood pressure.
- Laboratory evaluations including complete blood count (CBC), electrolytes, glucose, BUN, serum creatinine, calcium, magnesium, phosphorus, albumin, liver function tests, and INR.
- Assessment of PaO2.
- Complement studies of C3, C4, CH50. See above
- Assessment of peripheral blood T-cell and B-cell assays see above

Day 28 (or at hospital discharge if < 28 days):

- Brief history and physical exam to include vital signs and blood pressure.
- Laboratory evaluations including complete blood count (CBC), electrolytes, glucose, BUN, serum creatinine, calcium, magnesium, phosphorus, albumin, liver function tests, and INR.
- Assessment of PaO2.
- Complement studies of C3, C4, CH50.
- Assessment of peripheral blood T-cell and B-cell assays.

Day 60:

- Brief assessment of symptoms and documentation of adverse events, and a review of medical or surgical histories.

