**5.1.2 Potential Risks of Experimental Intervention**

Insertion of a central venous catheter for plasmapheresis:

Complications of this procedure include bleeding at the insertion site, pneumothorax, catheter-associated blood clots and infections (local and systemic). The complication rate of central vein catheters, inserted by physicians of variable experience, has been reported to be 15%.80

Plasmapheresis: The most common adverse effect is a drop in blood pressure associated with symptoms of dizziness or light-headedness79. Unusual complications include extracorporeal coagulation. The addition of citrate to the infusion solutions can lead to hypocalcemia with associated peri-oral tingling, numbness and more rarely muscle irritability, cardiac arrhythmias, and seizures.

Rare complications are infections by blood products (fresh frozen plasma (FFP)), transfusion reaction to FFP, an allergic reaction to the replacement solutions or sterilizing agents for the tubing, and adverse effects of immunosuppression produced by the associated hypogammaglobulinemia. Medications dosing may also need to be adjusted in patients being treated with plasmapheresis as certain medications can be removed by the procedure.

Rituximab:

The most common adverse effects (>10%) with rituximab from available clinical trials include74,78:

General: Fever (5% to 53%), chills (3% to 33%), headache (19%), pain (12%)

Dermatologic: Rash (1-15%), pruritus (5% to 14%), angioedema (1-11%)

Gastrointestinal: Nausea (8% to 23%), abdominal pain (2% to 14%)

Hematologic: Cytopenias (2-49%)

Neuromuscular & skeletal: Weakness (2% to 26%)

Respiratory: Cough (13%), rhinitis (3% to 12%)

Infusion Related: angioedema, bronchospasm, chills, dizziness, fever, headache, hyper-/hypotension, myalgia, nausea, pruritus, rash, rigors, urticaria, and vomiting; reactions (7-39%)

Less common adverse reactions (1% to 10%) include:

Cardiovascular: Hypotension (2-10%), peripheral edema (8%), hypertension (6% to 8%), flushing (5%), edema (<5%)

Central nervous system: Dizziness (10%), anxiety (2% to 5%), agitation (<5%), depression (<5%), hypoesthesia (<5%), insomnia (<5%), malaise (<5%), nervousness (<5%), neuritis (<5%), somnolence (<5%), vertigo (<5%), migraine (RA: 2%)

Dermatologic: Urticaria (2% to 8%)

Endocrine & metabolic: Hyperglycemia (9%), hypoglycemia (<5%), hypercholesterolemia (2%)

Gastrointestinal: Diarrhea (10%), vomiting (10%), dyspepsia (3%), anorexia (<5%), weight loss (<5%)

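### Exclusion 6 joins its three coagulation limits with 'and', so read literally it leaves patients past only one or two limits eligible for the central catheter, which does not serve the purpose given in section 3.2

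*Protocol*

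**What the plan says.** Protocol section 3.3, item 6, makes this an exclusion: "Coagulopathy defined as an INR > 1.8, PTT > 2 x control, and platelet count < 50K". The three limits are introduced as a definition and joined by 'and'. No 'or' or 'any of' appears, and the protocol does not define coagulopathy anywhere else.

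Section 3.2 gives the reason for the rule: "Patients with a coagulopathy are excluded to minimize the risk of catheter insertion associated with the intervention". It also describes the exclusions in general as meant "to exclude patients with increased risk for the associated intervention (corticosteroids, plasmapheresis and ritiximab".

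The catheter is part of the regimen for every subject. Section 2.2.1 says of plasma exchange and rituximab: "These latter two agents will require insertion of a dialysis/apheresis catheter into a central vein". Section 5.1.2 lists what can go wrong: "Complications of this procedure include bleeding at the insertion site, pneumothorax, catheter-associated blood clots and infections (local and systemic".

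Item 7 of section 3.3 has a similar construction for blood pressure: "uncontrolled hypertension (systolic BP > 160 mm Hg and diastolic BP > 100 mm Hg". Its stated reason is different: a contraindication to corticosteroids.

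**The concern.** An eligibility criterion has to give the same answer whoever applies it, and that answer has to match the reason the protocol gives for having it. Item 6 is doubtful on both counts. Taken at its word, it lets through a patient with, for example, INR above 1.8 and platelets below 50K, provided PTT is not above twice control. Such a patient would then have a large central venous catheter inserted, although section 3.2 says the exclusion exists to limit the risk of exactly that procedure.

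Taken as a loose list, item 6 excludes the same patient. Two careful screeners could reach opposite decisions and both point to the text. What is at stake is the safety of the people enrolled and a clear description of who the 10 subjects are.

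**Working it through.** No figure in the protocol needs reproducing. The check is a logical one.

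**Inputs**
- Three limits and their connector: section 3.3, item 6.
- Purpose: section 3.2.
- Catheter required: section 2.2.1. Insertion-site bleeding named as a risk: section 5.1.2.
- Laboratory tests: section 2.2.2, both the logged list and the Day 0 list.

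**Step 1: the two readings of item 6.** Each of three tests is either within or past its limit, so there are 2 × 2 × 2 = 8 patterns.

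| Limits passed | Patterns | Excluded if all three are needed (as written) | Excluded if any one is enough |
|---|---|---|---|
| None | 1 | 0 | 0 |
| One | 3 | 0 | 3 |
| Two | 3 | 0 | 3 |
| Three | 1 | 1 | 1 |
| Total | 8 | 1 | 7 |

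The readings disagree on 7 − 1 = 6 of 8 patterns. This counts kinds of patient. It does not say how often each kind occurs.

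**Step 2: does the text settle the connector?** Evidence points both ways.
- For the literal reading: item 6 is phrased as a definition, and the same list uses 'or' where it offers alternatives (items 3, 7, 9, 11 and 12).
- For the list reading: section 2.2.1 acts on one coagulation value alone, since replacement fluid changes when a subject's "INR is >1.5 at the initiation of a PEX treatment". Section 3.2's purpose also fits this reading better, because the literal rule sets no ceiling on any one value while another is within its limit.

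Neither side is conclusive.

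**Step 3: can item 6 be applied from the listed tests?** The Day 0 list in section 2.2.2 begins with a complete blood count and ends with "phosphorus, albumin, liver function tests, and INR". The list of logged monitoring tests also has blood count and INR. PTT is in neither. Taking the blood count to include platelets:
- If all three limits are needed, the listed tests can clear a patient (INR or platelets within limits) but can never establish the exclusion, because PTT is unknown.
- If any one limit is enough, the listed tests can exclude a patient on INR or platelets but can never fully clear one, again because PTT is unknown.

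PTT is therefore needed on either reading.

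**Step 4: item 7.** Two pressure limits give 2 × 2 = 4 patterns. Requiring both excludes 1, and requiring either excludes 3. The readings disagree on the 2 patterns with only one limit passed.

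**The case against.** The best defence is that 'and' here is ordinary list drafting. Clinicians would take each value as a separate reason not to place a catheter, and screening is done at one institution by investigators who are also the care team (sections 3.1 and 4.1). On that view no patient of the disputed kind would be enrolled. This may well be how the item was meant. It limits what can be said about consequences but does not cure the wording: the protocol never says so, and a criterion should not depend on the screener supplying the connector. PTT may also be measured in routine care, but the protocol does not list it.

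It is also fair to say that sections 3.2 and 3.3 are not two explicit rules in conflict. One gives a purpose and the other gives a definition that, taken literally, falls short of it. Section 3.2 speaks of catheter-insertion risk, not bleeding; bleeding comes in through section 5.1.2.

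Several stronger readings are tempting and are not supported.
- A reader might infer that bleeding in such patients would distort the primary safety endpoint. Section 2.3.1 assesses safety by PaO2 and by the need for vasopressors, inotropes or intravenous diuretics. Bleeding is not a component; it would be recorded as an adverse event and could reach the endpoint only indirectly.
- A reader might use the 15% catheter complication rate in section 5.1.2 to size the problem. That figure covers all complications, with operators of variable experience. It is not a bleeding rate or specific to coagulopathy, and section 5.5.2 commits to trained staff and ultrasound guidance.
- A reader might quote exact intervals for 0 or 1 event in 10 subjects. Those hold for any yes/no event in 10 people and do not measure the effect of the connector.
- A reader might infer that the historical controls become undefined too. Section 2.3.2 describes them only as hospital patients who had IPF exacerbations and does not say that they are chosen with the eligibility list.

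**Conclusion.** The point holds as a drafting defect in a stated eligibility rule. Read literally, item 6 excludes only patients past all three limits and leaves those past one or two eligible for the catheter, which does not serve the purpose in section 3.2. The text does not settle whether that reading was intended, and PTT, needed on either reading, is not among the listed tests.

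Its size in patients is unknown. The protocol gives no figure for how many candidates are past one or two limits only, and the number among 10 subjects could be zero. What can be stated is that the readings give opposite decisions for 6 of the 8 patterns. A reader might infer that patients at raised risk will in fact be enrolled; the protocol shows only that its wording permits it.

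Item 7 is secondary. Its 'and' is open to the same question, but its rationale concerns corticosteroids, and nothing in the protocol says that one pressure limit alone was meant to exclude.

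The conclusion rests on item 6 being the only definition of coagulopathy in the protocol and on the laboratory lists in section 2.2.2 being complete as to coagulation tests.

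**What to change.** - **Item 6:** reconcile sections 3.2 and 3.3 by stating in words whether any one limit or all three must be passed. The clinical team confirms which was intended. The three numeric limits stay as they are.
- **PTT:** if the criterion relies on it, add it to the baseline tests in section 2.2.2, with the result available when eligibility is decided.
- **Item 7:** state whether one or both pressure limits must be passed, again as the clinical team intends.

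The cost is a short amendment: a connector in each of two criteria and perhaps one added test. If the clarified wording excludes more patients than the literal one, there may be a few more screen failures. Section 3.1 reports 42 exacerbations in the past fiscal year for 10 places (42 / 10 = 4.2 per place, before eligibility and consent), so there should be room.

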**SECTION 4 – RECRUITMENT AND INFORMED CONSENT PROCEDURES**

**4.1 RECRUIMENT METHODS**

Participants will be recruited from the inpatient population at UPMC. Potential research subjects will be first identified by the study investigators, who are also the primary care physician/clinical care team. The clinician investigators will discuss the research project with the potential subjects or their legally authorized representatives as appropriate.

**4.2 INFORMED CONSENT PROCEDURES**

The consent process will begin via one of two possible pathways:

1) Referral of the prospective participant to the investigators/research coordinator by a physician who has knowledge of the proposed research, and obtains patient/surrogate consent for the research team to approach the patient/surrogate.

2) Individuals who have provided signed IRB-approved HIPPA compliant consent for participation in clinical trial research registries.

Prior to performing any of the study procedures the subjects must provide informed consent. The information about this study will be given to subjects in language understandable to subjects. Only physician investigators will present the study to the potential subjects. The physician investigator will verbally present a general outline of the research plan, including inclusion and exclusion criteria, to the prospective participant. The consent form, outlining the design of the study, will include the risks and benefits of participating, and will be reviewed and the investigator will answer any questions. Prospective participants may take as much time as required to make an informed decision. Written informed consent will be obtained from each participant prior to performing any research study procedures.

In addition, older potential study participants whose competency to consent is in question will be tested for sufficient comprehension and recall of the information presented. Prospective subjects who do not remember the important facts about participation in the research study after repeated testing will not be included in the study. The investigators will also assess whether a participant understands experimental procedures over time, including assessment throughout the full duration of participation in the study.

Proxy consent:Given the nature of the study population, which frequently requires mechanical ventilation with sedation, surrogate consent, will occur in a proportion of the study population. This will remain a valid consent until the patient is fully alert, and aware, and can provide a second consent to continue participation in the study.

**Criteria:** If subjects are able to communicate and follow simple instructions on mechanical ventilation, they will be asked to review the protocol and provide consent for participation. Subjects who are unable to demonstrate appropriate orientation to time, person and place as well as an acknowledgement of an understanding of the study design and potential risks, will be deemed unable to provide informed consent.

**Determination of Proxy:** When subjects are unable to provide informed consent, proxy consent will be obtained from the patient’s previously defined surrogate for medical decision-making. If no such surrogate exists, then the subject’s “next of kin” (spouse, children, and siblings, in that order) will be approached, consistent with UPMC hospital policy for obtaining consent for other medical procedures. Subjects judged to be “mentally incapacitated” will be allowed to participate in this study only after consent is obtained from a legal representative authorized to provide consent for research participation.

**Assent:** Once the subject who is incapacitated is able to provide informed consent, this will then be obtained. For mentally incapacitated subjects, assent will be obtained once the patient is extubated and able to communicate verbally. The patient or the surrogate, as identified in the manner outlined here, will sign the consent form prior to enrollment of the subject in the study.

